### Masking

Research staff responsible for collecting and entering of data for the cluster RCT will not be blinded to the identity of control or intervention wards, and the nature of the intervention precludes blinding among ward staff. For the observational sub-study, selection order will be masked from research staff until a list of eligible patients is compiled for each ward. Patients recruited to the observational sub-study will only be advised that the interview is part of study related to a larger research trial examining links between the hospital physical environment and patient outcomes. However, it is possible that some patients on intervention wards become aware of the intervention during the course of their admission.

### Statistical analysis

The analysis of primary outcomes will be with multi-level mixed effects generalised linear models using a Bernoulli family and logit link for the ‘proportion of patients who become fallers’ outcome and a negative binomial family and log link for the ‘rate of falls’ outcome. In these analyses, patient admissions will be nested within ward in the random effects part of the equation to take account of clustering of data by ward. The fixed part of the equation will examine group effects (intervention vs control phases) and adjust for time period. We will also adjust for seasonal effects on fall rates (that is, we will enter a covariate based on how many falls there were on each ward over the same time period over the previous 2 years). In relation to the observational sub-study, we will employ a full range of descriptive statistics to model the main features and distribution characteristics of the final data set. We will explore differences in patient sleep data and self-reported sleep and mobility behaviour collected over control and intervention periods through both qualitative and quantitative methods. Longitudinal data collected through actigraphy and environmental sensing will be subjected to exploratory analysis using pattern recognition and data filtering algorithms to classify the raw outputs against specific activity and event markers. Aggregated environmental sensing data will be graphically modelled through the development of scatter plots and histograms for visual identification of patterns and differences between control and intervention data. Categorical data on the causes of sleep disruptions collected through the patient interview tool will additionally be subjected to content [67] and thematic [68] analysis. Concurrently, we will undertake multi-level mixed effect generalised linear modelling with the quantitative data from the observational sub-study, using a Gaussian family and identity link for normally distributed continuous data. The random effects would be subjected to nested analysis; however, the fixed effect cannot adjust for seasonal variation, as we will not have access to any prior data of this nature.

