### Design of stepped wedge cluster RCT

The pilot trial will be undertaken across six RBWH wards (or clusters) and will be conducted over a 14-month period. The pilot cluster RCT will be of a ‘stepped wedge’ design [59], which differs in some important respects from the design of a conventional cluster RCT. A stepped wedge cluster RCT has clusters that provide both control and intervention data. This is achieved by implementing the intervention across all clusters recruited to the study. However, the sequence in which wards cross over from one condition to the other is randomly determined. In this study, all of our study wards will commence as controls at baseline. Figure 2 outlines the pattern in which study wards will transition from control to intervention phases. The first ward to transition to intervention phase will do so 2 months after study commencement and subsequent wards will transition to intervention phase at set intervals (or steps) of 2 months until all wards have transitioned from control to intervention phase. A further period of 2 months of data collection will be undertaken before the study is complete. Thus, all wards will provide a minimum of 2 months of control and intervention data. The stepped wedge cluster RCT design described here is increasingly seen as a suitable design for the pragmatic evaluations of patient safety [60, 61] and service delivery [62] interventions.

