### Wards and participants

We will recruit inpatient wards that are located at the RBWH campus (excluding an off-campus rehabilitation ward) with the highest reported rates of patient falls over the preceding 2 years. No specific limits will be applied to recruitment on the basis of service profile, patient demographics or diagnostic grouping. However, plans for ward closure or major physical refurbishments during the study period will be criteria for non-inclusion due to the potential for confounding effects on the pilot trial. Once study wards have been identified, an independent statistician will generate an implementation sequence using computer randomisation software. The sequence of transition from control to intervention phase will not be revealed en bloc and but rather one ward at a time and 2 months prior to the date of transition. This would mean that the first ward to transition from a control to an intervention phase will be revealed to the study team at baseline (month ‘zero’), with the transition to occur at the start of month ‘two’. Similarly, the second ward to cross over will be revealed at the start of month ‘two’ and cross over at the start of month ‘four’. This advance notification of wards due for transitioning to the intervention phase is necessary to allow adequate time for the hospital building and engineering services to complete and test the installations across all rooms in the ward (shared and single) in time for commencement of the intervention phase. Analysis of fall rates will be at the level of the ward and rely on data aggregated from patient incident reports completed by staff and from data coded routinely from the medical record for all admitted patients. A waiver from seeking individual patient-level consent for this component was sought and granted by the RBWH institutional human research and ethics committee.

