### Sample size

For the cluster RCT, we are constrained by the available funding as to the number of wards that can be included in the pilot trial (six) and period for which data can be collected (14 months), and hence, the overall anticipated sample is estimated to be approximately 7500 patients. While it is more usual for pilot studies to be conducted with smaller sample sizes, physical design change of this nature has never been undertaken within a stepped wedge cluster RCT. Due to the potential of a variety of operational and logistical challenges in installing new equipment over entire wards, we anticipate that the feasibility of such an approach will only be confirmed by undertaking a rolling sequence of ward installations. In this regard, installations in six wards would provide sufficient opportunities to elicit the full range of practical challenges that may be experienced and afford adequate time to test and modify our implementation approach. Hence, the larger sample size of the study can be considered a secondary feature of this pilot study rather than a primary goal. Within these sample estimates, it is possible to directly calculate the likely effect size that we can detect with 80 % power. Power for parallel cluster randomised trial designs can be calculated by using a conventional power analysis approach and then applying a multiplier to compensate for a design effect, taking the formula [1 + (*n* − 1)**p*], where ‘*n*’ = the number of subjects per cluster and ‘*p*’ = the intra-cluster correlation coefficient to take into account the dependency of observations within clusters [63]. However, the stepped wedge design additionally has a ‘within-cluster’ element (that is, all clusters provide intervention and control data), which provides power advantages to a parallel cluster RCT in a similar way to the comparison of paired with unpaired *t* tests. Hence, a power calculation specific to stepped wedge designs is required. One previously described approach highlights that stepped wedge designs could reduce the required sample size in cluster randomized trials [64], but is based upon the cohort style of stepped wedge design where individual participants are repeatedly measured across the length of the study. This is not consistent with our planned study, which reflects more a cross-sectional style of stepped wedge where individual participants are likely to only have one measurement for their involvement in the study. Fortunately, another power analysis approach based on the cross-sectional style of stepped wedge trial better suited for examining a dichotomous outcome (that is, for comparing patients who fall with those who do not) has been developed [65]. Using this approach, our study has 83 % power to detect an absolute reduction in the proportion of patients who are fallers (patients who experience one or more falls) from 5 % (in control) to 4 % (in intervention) assuming 1071 patients per time period (total *n* ≈ 7500), a coefficient of variation of 0.4, and using six clusters (wards), seven time periods (six steps plus baseline) and a two-tailed alpha of 0.05. This represents a 20 % relative reduction in the proportion of patients who become fallers. We anticipate that the minimum important difference for our intervention is likely to be lower than this since an effect size as low as 5 % relative reduction could still represent a cost-effective solution. Nonetheless, in line with the pilot aims of this trial (primarily focused on feasibility), statistical power and cost-effectiveness are not primary considerations and will be the focus of a subsequent main study if the main aims of this pilot trial are satisfactorily met.

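### The falls models name a ward random effect but no ward-by-period effect, so if fall risk drifts differently between the six wards the standard error of the lighting effect is too small

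*Protocol article*

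**What the plan says.** The design has six wards over 14 months: "The pilot trial will be undertaken across six RBWH wards (or clusters) and will be conducted over a 14-month period". One ward crosses over at a time, and "subsequent wards will transition to intervention phase at set intervals (or steps) of 2 months". The order is random: "an independent statistician will generate an implementation sequence using computer randomisation software" (Wards and participants).

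The Statistical analysis section gives a Bernoulli model with logit link for the proportion of fallers and a negative binomial model with log link for the rate of falls. For both, "patient admissions will be nested within ward in the random effects part of the equation to take account of clustering of data by ward". Fixed effects are phase, time period and a covariate built from each ward's falls in the same calendar period of the previous two years. No random effect below ward level other than the admission is named.

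On the unit of the fall-rate analysis, Wards and participants says: "Analysis of fall rates will be at the level of the ward and rely on data aggregated from patient incident reports".

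**The concern.** In a stepped wedge, much of the information on the intervention comes from comparing each ward with itself before and after its crossover, after removing a time trend shared by all wards. A ward random intercept allows wards to differ in average risk. It does not allow one ward's risk to move differently from the others' because of case mix, staffing or a cluster of repeat fallers. Such movement then counts as independent patient-level noise, and the standard error treats the roughly 178 patients in a ward-period as more informative than they are. The Bernoulli model for single admissions has no dispersion parameter to absorb the excess.

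Two things are at stake. The interval for the effect on falls could be too narrow, and its uncertainty feeds the economic model that is to underpin the decision to progress to a main trial. A ward-only model also yields no estimate of ward-by-period variance, which a stepped wedge sample size for the main trial would need, and supplying sample size inputs is a stated pilot objective.

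**Working it through.** **Inputs from the article.** Six wards and seven two-month periods ("seven time periods (six steps plus baseline) and a two-tailed alpha of 0.05"). Patient numbers: "assuming 1071 patients per time period", so 1071 / 6 = 178.5 per ward-period and 1071 × 7 = 7497 in total. Fallers: "from 5 % (in control) to 4 % (in intervention"; 5% is used under no effect. Between-ward coefficient of variation (CV): 0.4.

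**Assumption not in the article.** The CV *c* of fall risk between periods within a ward, beyond the common period effects. Range shown: 0 to 0.3.

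**The plan's own figures.** The only error rate given is the nominal two-sided 5%. The Sample size section also gives 83% power. The closed-form stepped wedge variance, with a ward SD of 0.02 and 178.5 patients per ward-period, gives a standard error of 0.00826 for the 0.01 difference, so z = 1.21 and power is about 23%. The formula returns 82.6% only if 1071 is taken per ward per period. That is a separate matter and nothing below depends on it.

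**Step 1: closed-form approximation.** Binomial variance of a ward-period proportion: 0.05 × 0.95 / 178.5 = 0.000266. Drift adds (0.05*c*)². If the model counts only the binomial part, the true variance exceeds the reported one by r = 1 + (0.05*c*)² / 0.000266, and the rejection rate is 2 × [1 − Φ(1.96/√r)].

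| *c* | added variance | r | 1.96/√r | rejection |
|---|---|---|---|---|
| 0 | 0 | 1.000 | 1.960 | 5.0% |
| 0.1 | 0.000025 | 1.094 | 1.874 | 6.1% |
| 0.2 | 0.000100 | 1.376 | 1.671 | 9.5% |
| 0.3 | 0.000225 | 1.846 | 1.443 | 14.9% |

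**Step 2: simulation of the faller model.** Logistic model with ward intercept and fixed periods, no effect, Wald |z| > 1.96, historical covariate omitted.

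| *c* | 101-point integration, 1600 runs | 81-point integration, 3000–4000 runs |
|---|---|---|
| 0 | 5.3% | 5.6% |
| 0.1 | 6.0% | 6.8% |
| 0.2 | 10.8% | 10.6% |
| 0.3 | 16.2% | 16.3% |

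A Laplace-type fit (1500 runs) that splits a total CV of 0.4 into stable and drifting parts agrees. With a stable share of variance of 1, 0.9, 0.8, 0.7 and 0.5 (so *c* = 0.4 × √(1 − share) = 0, 0.13, 0.18, 0.22 and 0.28), rejection is 5.9%, 8.2%, 9.7%, 12.0% and 16.5%. The cause is visible in the standard errors: the empirical SD against the mean model SE is 0.187 against 0.176 with stable wards, 0.209 against 0.174 at share 0.8, and 0.240 against 0.169 at share 0.5.

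**Step 3: fall-rate model.** A negative binomial model on ward-period counts with a ward intercept (500 runs) rejects 5.2%, 11.2% and 12.6% at shares 1, 0.8 and 0.5. The dispersion parameter does not fully absorb the drift.

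**Step 4: candidate remedies.** Adding a ward-by-period random effect to the faller model (300 runs, Monte Carlo error up to about 1.7 points) leaves Wald rejection at 6.0%, 9.3% and 9.7% at shares 1, 0.8 and 0.5. With a t distribution on 5 degrees of freedom this becomes 2.0%, 4.3% and 3.0%. A permutation test over the 6! = 720 ward orders stayed at about 4–6%.

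**The case against.** **The inflation is conditional.** A reader might infer that the planned test rejects 8–14% of the time as a matter of fact. The article does not support that. It gives no ward-by-period variance, and under its own planning model the test is near nominal. This stands.

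**Six wards as a defect in themselves.** A reader might also infer that a Wald test on six wards is materially anti-conservative even with stable risks. At the plan's CV of 0.4 the excess is about one percentage point or less. Coarse numerical integration can mislead here: a non-adaptive 15-point rule gives 7.1%, 8.0%, 13.1% and 19.1% at *c* = 0, 0.1, 0.2 and 0.3, and much of the apparent excess at *c* = 0 disappears with accurate integration. The Laplace-type fit did give 6.6% and 8.1% with stable wards at smaller ward CVs of 0.3 and 0.2, but those are not the plan's value.

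**The historical covariate.** It varies by ward and calendar period, so the plan does not assume that ward risk is constant apart from common period effects. The covariate helps to the extent that ward-specific swings recur each year. When the swings were simulated as independent between years, adding it brought no improvement (14.1% against 13.2% at *c* = 0.2, both from the coarse 15-point rule, so only the comparison is informative). How much it would absorb in practice is unknown.

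**What an article may leave out.** No standard-error method or small-sample correction is named. A condensed article may leave that to the analysis plan, so the omission is no finding. The point rests on the random structure that is stated.

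**Unit of analysis.** Reading the two sections as a contradiction goes too far. The sentence in Wards and participants mainly concerns data sources and the consent waiver. The nesting sentence covers two outcomes, one of which is naturally analysed per admission. A clarification is enough.

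**It is a pilot.** The Discussion places the trial's main value elsewhere than in statistical testing, and the Sample size section says power is not a primary consideration. This limits the consequence. It does not remove it, because the estimates and their uncertainty feed the economic model and the main-trial planning.

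**Conclusion.** The concern holds in conditional form. The stated random part has no term for ward-specific change over time. With stable ward risks the faller test is near nominal, at about 5–6%. With drift that the historical covariate does not capture, the standard error is too small, and rejection under no effect is about 6–7%, 11% and 16% at an assumed ward-period CV of 0.1, 0.2 and 0.3. These figures assume the plan's patient numbers, 5% fallers, ward CV 0.4, a Wald test and no benefit from the historical covariate. Confidence is high on direction and moderate on size. It is a worthwhile and cheap improvement to the pilot's analysis, and no threat to its feasibility aims.

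**What to change.** 1. Add a ward-by-period random effect to the faller model and to the fall-rate model, and report its estimated variance for main-trial planning.
2. Because that term alone leaves Wald rejection at about 6–10% with six wards, take the p-value and interval for the intervention effect from a permutation test over the 720 ward orders, which follows the randomisation used, or from a small-sample reference distribution such as t with few degrees of freedom.
3. State that the fall-rate model is fitted to ward-by-period or ward-by-month counts with log patient-days as offset, in line with Wards and participants.

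The cost is a few sentences of analysis text and a short program. Intervals widen. In the runs above the extra random effect raised the mean model standard error from 0.176 to 0.178 with stable wards (about 1%), from 0.174 to 0.183 at share 0.8 (about 5%) and from 0.169 to 0.197 at share 0.5 (about 17%). A t reference on 5 degrees of freedom widens the interval by a further 2.571 / 1.96 = 1.31 and was conservative in simulation (2.0–4.3%). Nominal power falls accordingly, which is acceptable in a pilot that does not rest on testing.

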**Methods/design:**

A stepped wedge, cluster randomised controlled trial will be conducted in six inpatient wards over 14 months in a metropolitan teaching hospital in Brisbane (Australia). The intervention will consist of supplementary night lighting installed across all patient rooms within study wards. The planned placement of luminaires, configurations and spectral characteristics are based on prior published research and pre-trial testing and modification. We will collect data on rates of falls on study wards (falls per 1000 patient days), the proportion of patients who fall once or more, and average length of stay. We will recruit two patients per ward per month to a concurrent observational sub-study aimed at understanding potential impacts on a range of patient sleep and mobility behaviour. The effect on the environment will be monitored with sensors to detect variation in light levels and night-time room activity. We will also collect data on possible patient-level confounders including demographics, pre-admission sleep quality, reported vision, hearing impairment and functional status.

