### Design of concurrent prospective observational sub-study

Detailed patient-level outcomes will be measured by systematic sampling across participating wards throughout the pilot trial as part of a prospective observational sub-study. One patient per ward per month will be recruited from all six included wards (*n* = 84) and we will collect data through a combination of self-report and continuous monitoring, the details of which are described under the ‘outcome measures’ section of this protocol. Written consent will be secured prior to participant recruitment. Patient eligibility will be established by the study research officer (RO) in consultation with the ward nurse manager or shift coordinator at each recruitment point. The RO will be responsible for securing participant consent. Some inclusion/exclusion criteria will apply to recruitment. We will exclude patients who have been admitted for longer than 30 days or are due to be discharged within the following 3 days. Patients that have been recruited to the current study in a previous month will also be ineligible for recruitment. Patients with known cognitive impairment will be excluded, as an important element of this sub-study is to capture data on participant subjective experiences and this would be infeasible among cognitively impaired patients. Due to lack of multi-language versions of the scales used in this study, we will also exclude patients who are not fluent in English. We will exclude patients who are unstable or deemed too unwell to participate. Finally, patients aged less than 65 years on the day of recruitment will also be considered ineligible for recruitment.

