Prior to the start of the study, the principal investigator (PI) will produce 84 sets of computer-generated random integer sequences ranging from ‘1’ to the maximum number of bed locations in any ward, for example, ‘35’. These will then be printed and placed in sealed opaque unmarked envelopes and handed over to a RBWH Safety and Quality Unit (SQU) staff member who is not involved with the study. At each recruitment point, the RO will identify, in consultation with ward nursing managers, patients who are eligible to be approached for the study and a list of eligible bed numbers will be compiled and communicated to the nominated SQU staff member. The staff member will then open one envelope and will generate the order of recruitment as per the number sequence in the envelope. This list will be provided to the RO for commencement of recruitment. The PI will monitor recruitment to ensure adherence to the recruitment protocol. The RO will approach the first bed number on the recruitment order; if a patient does not consent to participate in the study, this process will continue until a patient is successfully recruited. This process will be replicated for each ward at every recruitment point.

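### The sub-study models are wrongly said to be unable to adjust for season, and no time-period term is named for them, although the design allows one

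*Protocol article*

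**What the plan says.** The Statistical analysis section gives the falls models two separate calendar-time terms. The first is time period: "The fixed part of the equation will examine group effects (intervention vs control phases) and adjust for time period". The second is a seasonal covariate built from each ward's falls over the same part of the year in the previous two years.

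For quantitative sub-study data it plans a mixed model with a Gaussian family, an identity link and nested random effects. It then says that "the fixed effect cannot adjust for seasonal variation, as we will not have access to any prior data of this nature". No time-period term is named for this model.

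The sampling scheme is set out elsewhere. "One patient per ward per month will be recruited from all six included wards" (Design of concurrent prospective observational sub-study), and "This process will be replicated for each ward at every recruitment point". The trial has six wards over 14 months. At the start, "all of our study wards will commence as controls at baseline"; one ward crosses over after 2 months, and "subsequent wards will transition to intervention phase at set intervals (or steps) of 2 months" (Design of stepped wedge cluster RCT).

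**The concern.** In a stepped wedge design, control observations come early and intervention observations late. A contrast without a calendar-time term therefore takes up whatever else changed over the 14 months.

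The sub-study outcomes are plausibly sensitive to time of year: sleep, light dose and overnight room light levels. The Intervention section itself sets the lights' operating hours with seasonal changes in sunrise and sunset in mind.

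The protocol treats the adjustment as impossible for want of prior data. An analyst who takes that at face value would leave calendar time out. A seasonal or secular change could then be read as an effect of the lighting on the mechanisms that the Discussion wants the pilot data to test.

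**Working it through.** **Inputs from the protocol.** Six wards, 14 months, one ward crossing over every 2 months, one patient per ward per month. This reproduces the stated sample: 6 × 14 × 1 = 84. (The Abstract says "We will recruit two patients per ward per month to a concurrent observational sub-study", which would give 168. That conflict is a separate point. The mean months and the correlation below do not depend on it, but the standard errors do; I use 84.)

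**Assumptions.** The protocol gives no ward ICC, outcome SD, seasonal amplitude or drift. I take ICC 0 to 0.10, one summary value per patient, a time pattern common to all wards, and a true intervention effect of zero.

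**Overlap in time.** Ward i (i = 1 to 6) crosses over at month 2i. The share of wards under intervention in the seven periods is 0, 1/6, 2/6, 3/6, 4/6, 5/6, 1. Five periods contain both conditions, so period effects and the intervention effect can be estimated together. The 84-row design matrix has full rank with 2-month period indicators, with month indicators, and with an annual sine/cosine pair plus linear trend.

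**Separation in time.** Ward i has 2i control months with midpoint i, and 14 − 2i intervention months with midpoint i + 7.
- Control observations: Σ2i = 42; mean month Σ(2i × i)/42 = 182/42 = 4.33.
- Intervention observations: Σ(14 − 2i) = 42; mean month Σ(14 − 2i)(i + 7)/42 = 406/42 = 9.67.
- The correlation of intervention status with month is 0.66.

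**Bias if no time term is entered.** The bias is the intervention element of (D′V⁻¹D)⁻¹D′V⁻¹s. Here D holds the intercept and intervention status, V has exchangeable correlation within ward, and s is the time pattern (a linear drift, or a 12-month cosine of amplitude A over all phases). At ICC 0 the drift bias is simply (9.67 − 4.33)x = 5.3x.

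| Assumed ICC | Drift of x per month | Annual cycle, worst phase | SE, no time term (SD) | SE, period terms (SD) | SE ratio |
|---|---|---|---|---|---|
| 0 | 12 × 0.444 = 5.3x | 0.48A | 0.218 | 0.293 | 1.34 |
| 0.05 | 12 × 0.494 = 5.9x | 0.53A | 0.224 | 0.315 | 1.41 |
| 0.10 | 12 × 0.520 = 6.2x | 0.56A | 0.224 | 0.323 | 1.44 |

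With the seven period effects, both biases are zero.

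**What this could do to a test.** Take ICC 0 and an assumed A of 0.5 SD at the worst phase. The bias is 0.478 × 0.5 = 0.239 SD against an SE of 0.218, and a nominal 5 % two-sided test rejects about 19 % of the time (22 % at ICC 0.05). For A = 0.25 SD the figures are 8.5 % and 9 %. These are normal approximations.

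**Alternative adjustments.** A sine/cosine pair alone removes a pure 12-month cycle cheaply (SE 0.243 at ICC 0.05, 9 % above 0.224). But it leaves a drift bias of 12 × 0.363 = 4.4x at ICC 0, up to 12 × 0.436 = 5.2x at ICC 0.10. Adding a linear trend removes both biases, with SEs of 0.291, 0.313 and 0.320, about the same as for period effects.

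**The case against.** The strongest reply is textual. The falls models have a time-period term and, separately, a seasonal covariate defined by historical falls. The remark about lacking prior data fits the second. On that reading only the historical covariate is dropped, and a time-period term may still be intended; a condensed article may leave the full model to a fuller document. This stands in part. A reader might infer that the sub-study contrast is certainly confounded with calendar time, but the protocol does not say that time period is omitted, so the bias is conditional on that. What survives on either reading is that the sentence is wrong: a model with period terms does adjust for season common to all wards.

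A reader might also infer larger biases from the fact that the two phase midpoints are exactly 7 months apart in every ward. That gives 7x for drift and up to 0.63A for a cycle, but only with fixed ward effects. The protocol plans random effects, for which the smaller figures apply.

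Finally, it may be said that little depends on this. The Objectives make feasibility the primary aim, the Discussion places the pilot's value outside its statistical tests, the sub-study comparisons are framed as exploratory, and the limitation is disclosed. All of that is fair and lowers the severity. It does not remove the point, since the disclosed limitation is one that the design need not have.

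**Conclusion.** The stated reason for not adjusting for season is incorrect, and the protocol leaves open whether time period enters the sub-study models. If it does not, the bias is 5.3x to 6.2x for a common drift and up to 0.48A to 0.56A for a common annual cycle, assuming random ward effects and an ICC of 0 to 0.10. Whether that is material cannot be judged from the protocol, which gives neither x nor A; the cycle figures are for the least favourable phase.

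This should be fixed but is not critical. The falls analysis already adjusts for time period and is unaffected, and no confirmatory conclusion rests on the sub-study.

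**What to change.** Delete the clause saying that season cannot be adjusted for. State that the sub-study models include time period (the seven 2-month periods) as a fixed effect, as the falls models do, and that only the historical covariate is unavailable. Add an annual sine/cosine pair plus linear trend as a sensitivity analysis. The pair alone is not enough, because it leaves most of any drift bias.

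This takes a line or two of wording and no new data. The cost is precision: with 84 patients the SE of the intervention effect rises from about 0.22 SD to 0.29–0.32 SD, or 34 to 44 %. Seasonal patterns that differ between wards would remain unadjusted, and the text should say so.
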